### Outcome measures

#### Primary outcome measurement

PSQI (19) assesses the sleep quality of the subjects, and HAMA (20) assesses the anxiety severity of the subjects and is jointly used to evaluate the effect of combined treatment. The evaluation time points are in the baseline period (week 2), the trial period (weeks 3, 6, 9, and 12), and the follow-up period (weeks 6 and 12).

#### Secondary outcome measurements

ISI (21) evaluates the severity of subjective insomnia for 2 weeks, GAD-7 (22) can evaluate the degree of anxiety symptoms within 2 weeks and is jointly used to evaluate the degree change of anxiety insomnia. The evaluation time points are the same as the primary outcome index.

#### Safety evaluation

In the process of this research, researchers should monitor and record the adverse events or emotional reactions of subjects, and analyze the causal relationship between the combination treatment and the severity of the adverse events in time (23). During the trial, any adverse events (defined as falls, sprains, any sports-related injuries, etc.) will be recorded. If an adverse event occurs, and the subject has emotions such as mania, severe depression, extreme depression, etc. The experiment should be terminated in time, and psychological counseling or medication should be immediately accepted.

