Natural, focused awareness appropriate speed and outstanding style	1–3 marks will be deducted for minor deviations from the requirements, 4–6 marks for significant deviations and 7–10 marks for serious deviations.
Forgetting the action	3–5 marks will be deducted for each instance of forgetfulness, depending on the degree.
Out of balance	1 point for each wobble; 2 points for each support; 3 points for successive supports.
Number of movements	3 marks will be deducted for each extra or missing movement.
Direction of movement	One point for each deviation of 45° or more from the prescribed direction.
Repeat the set	If the examination is interrupted due to forgetfulness or mistakes, the examination may be repealed once and 10 points deducted, and so on.
Unfinished sets	Those who do not complete the routine will not be graded and will be marked as failing.

A total of 100 points will be awarded, with a total score of less than 60 being unqualified.

Group A receives combined treatment 30 min before sleep. First, 24-style Taijiquan training will be performed for 15 min each time, once a day. Then do acupoint pressing at Baihui (DU20), Shenting (DU24), Yintang (EX-HN3), Shenmen (HT7), and Sanyinjiao (SP6), kneading 1∼2 times for 1∼2 min. And then replacing with the next acupoint, each acupoint will be kneaded 1∼2 back and forth, a total of 15 min of continuous pressing. After each treatment, study members should make strict records to ensure the full participation of subjects in the study (18). Group B does the therapy of Taijiquan combined with acupoint pressing 30 min after waking up, and the treatment procedures and methods are the same as those of Group A. Group C will not accept any intervention on Taijiquan or acupoint pressing, and maintain their normal lifestyle. After the study, subjects in this group can choose to participate in the treatment of 24-style Taijiquan training combined with acupoint massage.

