### Follow-up

The purpose of follow-up is to evaluate the long-term effect of Taijiquan combined with acupoint pressing. After completing the treatment, a follow-up evaluation will be performed on the 15th, 18th, 21st, and 24th weeks. Participants will not accept any intervention but only complete the same scales as the trial period during the follow-up period. To encourage participants to comply with the rules, we will give special care to each participant and pay close attention to the changes in their sleep quality.

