Our research has the following advantages. First of all, to ensure the quality of the study and reduce the influence of confounding factors, the research team will conduct a baseline assessment of the subjects. The subjective evaluation results will be obtained by using PSQI, HAMA, Generalized anxiety scale (GAD-7), and Insomnia Severity Index (ISI). The emotional changes of the subjects during the experiment will be recorded objectively by the study members (29). Through the analysis of a large number of papers, Baihui, Sanyinjiao, Shenmen, Yintang, and Shenting are recognized as acupoints with good curative effects in the treatment of insomnia (30–32). This experiment does not use skin-breaking intervention, but self-acupoint pressing intervention to ensure the safety and controllability of the trial to a certain extent, and increase the feasibility of the trial. Secondly, the subjectivity of the subjects in this experiment is strong. To ensure the validity of the experimental research data and reduce the deviation caused by the amount of operation or non-standard operation, senior acupuncture and massage lecturers and Taijiquan professional teachers are arranged to conduct regular acupoint pressing and Taijiquan training for the subjects so that the subjects can carry out the standard operation in the prescribed treatment period. In addition, most of the subjects in this experiment have a certain tendency toward anxiety and depression. To maintain the physical and mental health of the subjects and ensure that the subjects could complete the research experiment, the research team specially equipped professional psychological counselors to carry out regular psychological counseling, and the researchers recorded their emotions to prevent overreaction in the research process. In the course of the experiment, the research team will collect the subjective scale data and objective emotional records of the subjects every 3 weeks, and analyze the effectiveness and difference of Taijiquan combined with acupoint pressing therapy in treatment groups and control group (33, 34). After 12 weeks of intervention, all participants will begin an unsupervised follow-up period of another 12 weeks to restore their daily lifestyle and re-use the results of the scale to analyze the long-term effect of combined therapy. In Chinese clinical research trials, the effects of Taijiquan and acupoint pressing in the treatment of insomnia will vary with different intervention times, so the intervention time in this experiment is also the expansion angle of the combined therapy, which will also be the focus of this study report.

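### The only stated termination rule requires an adverse event and a severe emotional state together, so read literally, mania or severe depression alone does not trigger it

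*Protocol article*

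**What the plan says.** Four statements in the Safety evaluation section of the protocol article matter here.

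- Monitoring: "researchers should monitor and record the adverse events or emotional reactions of subjects".
- Definition: "any adverse events (defined as falls, sprains, any sports-related injuries, etc.) will be recorded".
- Condition for stopping: "If an adverse event occurs, and the subject has emotions such as mania, severe depression, extreme depression, etc". A full stop follows, so the clause has no consequence of its own.
- Action, in the next sentence: "The experiment should be terminated in time, and psychological counseling or medication should be immediately accepted".

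No other section of the article states a condition for terminating or discontinuing. Other sections do touch on emotional safety:

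- The inclusion and exclusion criteria keep out people with severe depression, suicidal tendency or severe mental disorders, but only at entry.
- The Abstract gives regular counseling to all three groups and has safety evaluated at each assessment.
- The Discussion says that professional counselors are provided and that subjects' emotions are recorded.

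**The concern.** The sentence is a participant-safety rule, and the foreseeable serious event in this population is psychiatric. Entry requires a HAMA score of at least 14, and the Discussion says that "most of the subjects in this experiment have a certain tendency toward anxiety and depression". One would expect the onset of mania or severe depression to be enough to stop a subject's participation in the intervention and start treatment. As written, the rule also asks for an adverse event, a term that the section illustrates only with physical injuries.

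At stake is how clear the instruction is to site staff. A person who follows the text literally finds no trigger for the one event that the prescribed remedy addresses. The analysis of the outcomes is not affected.

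**Working it through.** No arithmetic applies. The check compares the statements in the Safety evaluation section and asks which situations meet the condition.

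**Step 1: the literal rule.** Joining the broken clause to the sentence after it gives: adverse event AND severe emotional state → terminate, with counseling or medication.

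**Step 2: does an adverse event already include the emotional state?** Two features of the section suggest that it does not. The monitoring sentence lists adverse events and emotional reactions as two things joined by *or*. Every named example of an adverse event is physical (falls, sprains, sports injuries). One feature leaves it open: the list of examples ends in *etc.*

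**Step 3: the four possible situations under three readings.**

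| Adverse event (physical) | Severe emotional state | Literal *and*, narrow adverse event | Emotional state counted under *etc.* | *And* replaced by *or* |
|---|---|---|---|---|
| yes | yes | met | met | met |
| no | yes | **not met** | met | met |
| yes | no | not met | not met | met |
| no | no | not met | not met | not met |

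The first two readings differ in one row only, the psychiatric state without an injury. That row is the whole of the point.

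**Step 4: which reading fits the remedy?** Counseling or medication answers an emotional state and does not answer a sprain. The remedy therefore fits a rule in which the emotional state is sufficient. The literal reading adds a second requirement to which the remedy has no relation.

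**Step 5: would swapping the conjunction be enough?** It would repair the second row. It would also make any fall or sprain, however minor, a reason to terminate and give psychological care (third row). Two separate clauses are better than one changed word.

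**Step 6: does other text supply the trigger?** The entry criteria act before randomization. Counseling and the recording of emotions are support and monitoring. None of them says when to stop.

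**The case against.** The strongest objection is that the rule has to be rebuilt from broken English before anyone can fault its conjunction. The conditional clause stops without a consequence, and awkward phrasing recurs elsewhere in the article. The intended meaning can be recovered from the remedy, which makes this look like an editorial matter. This stands as an explanation: a translation slip is the likely cause. It does not remove the problem, because the published sentence is the only termination rule that the article gives.

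Second, the open *etc.* could take in mania or severe depression, and the psychiatric event would then satisfy both halves by itself. That reading is possible. It is not the natural one next to the separate naming of emotional reactions, and staff should not have to infer it.

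Third, a rule of the form *if both, then stop* does not tell anyone to continue when only one is present, and sensible staff would probably act. This is correct. The defect is an unclear trigger, and no wrong action is directed.

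Fourth, counseling for all three groups, the recording of emotions and the entry exclusions reduce the practical risk. This also stands, although none of them is a stopping trigger.

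A reader might be tempted to go further in three ways that the article does not support.

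- *The rule cannot operate in group C or during follow-up, because no study exercise takes place there.* The Interventions section says "Group C will not accept any intervention on Taijiquan or acupoint pressing, and maintain their normal lifestyle" and the Follow-up section says "Participants will not accept any intervention but only complete the same scales as the trial period during the follow-up period". Nothing in the safety section requires an adverse event to arise from study exercise. Falls and sprains happen to anyone, so the wording works the same way in those settings.
- *Emotional reactions are never assessed for causality.* The section asks researchers to "analyze the causal relationship between the combination treatment and the severity of the adverse events in time". Whether that leaves emotional reactions out depends on the same narrow reading of *etc.*, so it is not an independent finding.
- *The trial has no psychiatric withdrawal criterion.* The full protocol is not shown and may contain one.

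**Conclusion.** The point holds as a wording defect in a stated safety rule. Read as written, severe psychiatric deterioration without another adverse event does not meet the article's only termination trigger, although the prescribed remedy is meant for that state. The conclusion rests on two assumptions: that the broken clause and the sentence after it form one rule, and that adverse events are understood through the physical examples given.

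Its size cannot be estimated. The article gives no rate of mania or severe depression, and no number of affected participants is claimed. Nor is any effect on estimates, power or type I error. The change is still worth making, because the rule protects participants and is almost free to correct.

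**What to change.** Replace the rule in the Safety evaluation section with two clauses.

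1. *Psychiatric clause.* If a subject in any group develops mania, severe or extreme depression, or a similar state, whether or not another adverse event has occurred, that subject's study intervention (if any) is stopped and psychological counseling or medication is given immediately. The state is recorded as an adverse event, and scheduled outcome assessments continue where the subject agrees.
2. *Physical clause.* Falls, sprains and other injuries are handled under their own rule.

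Three details of the first clause matter. Study intervention should mean Taijiquan and acupoint pressing, so that counseling continues; *if any* covers group C, which does neither. Naming the subject settles whether one person's intervention or the whole trial is to be stopped, which the present text leaves open. Stopping the intervention without ending assessment keeps outcome data in a trial that plans to analyze by intention to treat.

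The cost is one sentence split into two clauses and one item added to what counts as an adverse event. The design, sample size and analysis do not change.

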#### Quality control and data collection and management

All researchers will receive a series of training before the start of this study, to ensure that they fully understand the study protocol and standard procedures. CRFs labeled by unique numeric identifiers will be used to collect relevant data, adverse events, and safety assessments for participants. Only outcome assessors have access to CRFs and will perform the double data entry (24, 25). The Evidence-based Medicine Center of the Chengdu University of TCM will be in charge of supervising the study and monitoring data every 3 weeks.

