## Methods

### Study design

This proposed study is a multi-centered, single-blinded, randomized non-pharmacological therapy trial with the assessor and statistician blinded to treatment allocation, evaluating the effect of Taijiquan combined with acupoint pressing in the treatment of college students with anxiety insomnia, and finding the best treatment time (12). The research team will include patients with anxiety insomnia according to the international diagnostic criteria DSM-5 (13). A total of 126 participants who have passed the professional psychological assessment will be enrolled in this trial from the universities in Chengdu, Sichuan Province. They will be randomly divided into treatment group A (treat before sleep), treatment group B (treat after sleep), and control group C (waiting list group) in the ratio of 1:1:1. The whole treatment process will be completed under the guidance of professional doctors and teachers of Chengdu University of Traditional Chinese Medicine in Sichuan, China. This test will be reported following the Comprehensive reporting Test Standard (CONSORT) statement (14). The flow chart of the trial is shown in Figure 1, and the schedule for registration, intervention, and evaluation is shown in Figure 2.

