### Randomization and blinding

After the participants completed the baseline evaluation, they were randomly divided into treatment group A (treat before sleep), treatment group B (treat after sleep), and control group C (waiting list group) according to the proportion of 1:1:1. The random allocation sequence will be generated and hidden by the PLAN program using the statistical software SAS9.1. The random packet sequence is hidden by opaque and sealed envelopes, and the data statistician will not know the result of the allocation (15). This process ensures the full concealment of randomization and is not affected by the experimenter or subjects. Random assignments will be made after the first visit to participants who provide informed consent and meet the inclusion criteria. If the participant is eligible to be included in the study, the researcher will open the corresponding envelope in front of the participant. Envelopes will not be issued until all subjects have completed the baseline assessment. The subjects could not be blinded because of the unique nature of the intervention, but to ensure the scientific nature of the trial, the research team blinded trial evaluators and data, statistical analysts (16). To avoid misleading data analysts, researchers and subjects will be controlled to communicate with them to ensure that later data results are not affected by the subjective judgment.

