
This study has certain limitations. The research team cannot use the blind method for the test subjects, so the test process adopts the random distribution sequence results. The test treatment period and grouping process are confidential to the subjects, and the evaluators and data statistical analysts are blinded (35). The random distribution information cannot be disclosed until the research and test are completely completed. At the same time, subjects are not allowed to communicate treatment measures with each other during the trial, so as not to increase the influence of confounding factors.

This experimental study will collect experimental data from subjective and objective to analyze the effectiveness of Taijiquan combined with acupoint pressing in the treatment of anxiety insomnia of college students. It is of great significance for clinical practice to find the best time for the treatment of anxiety insomnia in college students (36). The results of the follow-up data of subjects are also expected to evaluate the effectiveness of Taijiquan combined with acupoint pressing as adjuvant therapy or preventive intervention of specific health status in the treatment of clinical anxiety insomnia.

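### The CRF access rule puts possibly arm-revealing adverse-event pages in the blinded assessors' hands, and the Discussion wrongly calls allocation confidential to participants

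*Protocol article*

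**What the plan says.** **Assessors.** Under Study design, the trial is described as run "with the assessor and statistician blinded to treatment allocation". Randomization and blinding repeats that "the research team blinded trial evaluators and data, statistical analysts", and the limitations paragraph of the Discussion says so again.

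**CRFs.** Under Quality control and data collection and management, numbered CRFs "will be used to collect relevant data, adverse events, and safety assessments for participants". The next sentence sets an exclusive rule: "Only outcome assessors have access to CRFs and will perform the double data entry". Safety evaluation gives falls, sprains and sports-related injuries as the adverse events. It has researchers record them and analyse whether the combined treatment caused them.

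**Participants.** Randomization and blinding says: "The subjects could not be blinded because of the unique nature of the intervention". It adds that "the researcher will open the corresponding envelope in front of the participant". The Discussion, describing how the trial copes with unblinded participants, says: "The test treatment period and grouping process are confidential to the subjects, and the evaluators and data statistical analysts are blinded". It also bars release of the allocation until the study is over.

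**Outcomes.** PSQI and HAMA are jointly primary. The article does not say who rates HAMA. Follow-up has participants completing the same scales as in the trial period.

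**The concern.** Participants know their arm and the comparator is a waiting list, so blinding of the assessors is the main protection that the plan offers against biased outcome rating. An assessor who must also handle and enter safety data may see information that points to an arm. That matters for any scale the assessor rates. For any scale the participant completes, assessor blinding gives no protection in the first place.

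The Discussion sentence raises a different problem. It offers, as a remedy for unblinded participants, a confidentiality that the trial's own procedure rules out. A reader could then credit the trial with a safeguard it does not have.

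**Working it through.** The plan gives no figure on this point, so the check is mainly a comparison of statements, followed by a small calculation of how informative an adverse-event entry can be.

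**1. Assessor blinding against the CRF rule**

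- Claimed in three places: assessors are blind to allocation.
- CRF content: adverse events and safety assessments are included.
- CRF access and entry: outcome assessors, and nobody else.
- Event definition: falls, sprains and sports-related injuries, with causality considered against the combined treatment.
- Exposure (Interventions): groups A and B do Taijiquan and acupoint pressing daily for 12 weeks; group C does neither.

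It follows that the blinded role is assigned the safety pages by an explicit rule. A sports injury points towards A or B. A recorded judgement that the combined treatment caused an event would point there more strongly, if it is kept on the CRF, which the article does not say. Neither separates A from B, since both do the same activity.

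The rule also fits poorly with two other statements: researchers, not named as assessors, record the adverse events, and an evidence-based medicine centre monitors the data every 3 weeks.

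**2. How much an entry, or its absence, tells the assessor**

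With 1:1:1 allocation of 126, there are 42 per arm, so 84 of 126 (66.7%) are active and 42 of 126 (33.3%) are controls. The article gives no injury rates. Let a be the proportion with an event in the active arms and c the proportion in controls.

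*No event.* P(control | no event) = (1/3)(1 − c) / [(1/3)(1 − c) + (2/3)(1 − a)]. Taking c = 0, the value that makes absence most informative for a given a:

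| Assumed a | Calculation | P(control given no event) |
|---|---|---|
| 5% | 0.3333 / (0.3333 + 0.6333) | 34.5% |
| 10% | 0.3333 / (0.3333 + 0.6000) | 35.7% |

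Against a starting value of 33.3%, absence is almost uninformative.

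*Event present.* P(active | event) = 2a / (2a + c). If c = a, this is 2/3, or 66.7%, so nothing is learned. If c = a/2 (an assumption), it is 2 / 2.5 = 80%. If c = 0, it is 100%. An entry can therefore range from uninformative to decisive, depending on rates the article does not give.

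*How many participants.* At a = 5% or 10%, the expected number of active participants with an event is 84 × 0.05 = 4.2 or 84 × 0.10 = 8.4.

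**3. Participant confidentiality**

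- Participants recruitment: the groups and the interventions are explained to candidates.
- Randomization and blinding: participants cannot be blinded, and the envelope is opened before them.
- Interventions: they practise before sleep, after waking, or not at all.
- Discussion: treatment period and grouping are confidential to them.

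A participant who sees the envelope opened and then follows the arm's schedule knows the arm. The last statement cannot stand with the other three.

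**The case against.** **Controls have accidents too.** This is correct. The event definition is not limited to treated participants, and group C keeps its usual lifestyle. A reader might infer that an injury entry identifies a Taijiquan participant, that its absence marks a control, and that assessor blinding is therefore undone. The documents support none of these. An entry suggests an arm only to the extent that rates differ, absence carries almost no information, and only a few participants would be affected.

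**CRF layout is operational detail that an article may leave out.** This would be a good answer to silence, but the article is not silent. It states that only the assessors have access. A separate safety form handled by other staff, if the full protocol has one, would conflict with that rule as written.

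**Single-blind is already defined.** This also stands. Study design ties the term to assessor and statistician, and the Discussion lists unblinded participants as a limitation. A reader might conclude that the label itself misleads, but the article nowhere claims that participants are blinded to treatment under that label.

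**The Discussion sentence may only mean that the sequence was concealed.** This is plausible for the word grouping and for the bar on releasing the allocation. It does not explain why the treatment period is also called confidential to participants.

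**HAMA may not be assessor-rated.** The article leaves this open, and its follow-up wording, read literally, has participants completing every scale. Any statement about bias in HAMA must therefore be conditional.

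**Conclusion.** The concern holds in two limited parts.

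First, the CRF access rule weakens the assessor blinding that the article claims in three places. The effect is confined to participants with an adverse event and to scales that an assessor rates. It cannot distinguish A from B. If it biases anything, the likely direction is in favour of the active arms over the waiting list, but the amount cannot be derived from the document. The conclusion assumes that the access rule is meant literally and that safety pages are not kept apart; nothing in the article says that they are.

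Second, the Discussion's statement on confidentiality towards participants contradicts the randomization procedure and is wrong as written. It changes no procedure or estimate, but it describes a safeguard that does not exist.

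A reader might also suppose that attendance or treatment logs sit on the assessors' CRF. The article does not say so: session records are kept by study members. Sample size, visits and analysis are unaffected. Both parts should be corrected, and neither is fatal to the design.

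**What to change.** 1. **Quality control and data collection and management.** Replace the access rule. Assessors see and enter only the outcome scales. Adverse-event and safety pages, including any causality judgement, go on a separate form completed and entered by the unblinded study members who already record the sessions. Group C has no sessions to record, so use the same form in all three arms at each assessment. Reconcile the wording with the researchers' role under Safety evaluation and with the 3-weekly monitoring.
2. **Discussion, limitations.** Correct the sentence so that confidentiality applies to assessors, to analysts and to the sequence before assignment, not to participants' own allocation.
3. **Outcome measures.** State who rates HAMA. State that any participant-completed scale is unblinded self-report compared with a waiting list, so that assessor blinding is not read as covering it.

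The cost is one additional form, an access rule and some wording. Existing staff can carry it out, and the downside is slightly more data handling.
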